### Compliance and participant retention

Compliance refers to whether or not an individual conforms to the recommendations of the prescribed dosage, timing and frequency of an intervention [22].

Participants of both groups will be told initially and during group training sessions throughout the study that compliance to exercises are important and will improve their odds of recovery. They will be told that compliance consists of performing the prescribed number of repetitions, the pulling force and the TUT.

Using BandCizer™ could improve compliance as the participants know that their performance is being recorded. The feedback group receives visual feedback and auditory guidance from the iPad when performing the exercises and have access to a calendar with the planned training sessions. The visual feedback consists of a vertical bar that moves from side to side on a horizontal bar at the same pace as the predetermined TUT. When the elastic band is stretched the horizontal bar is being filled with colour and the participant has to keep up with the vertical bar to perform the exercise with the prescribed TUT and pulling force (Fig. 4). The auditory guidance consists of a voice that counts the seconds of each contraction phase. The control group has access to the calendar as well, however they only receive visual and auditory feedback on pulling force and has no vertical bar to keep up with during the repetitions (Fig. 5). Both groups are asked to record pain on a 100 mm VAS scale before and after each exercise.

**Fig. 4 Fig4:**
[figure not shown]
BandCizer-app with feedback on TUT

**Fig. 5 Fig5:**
[figure not shown]
BandCizer-app without feedback on TUT

All group training sessions will be planned before the intervention starts for all participants. If they are unable to attend any of the sessions, they are asked to contact the primary investigator by phone or e-mail and they will then be instructed to do the exercises at home instead. If any participant fails to show up for a training session and did not cancel beforehand they will be contacted by the primary investigator and asked in a friendly manner if they will return to the next group training session and they will be asked to do the missing training session at home.

### Information and patient education

Participants will be instructed not to do any type of other strengthening exercises for the lower extremities during the intervention and not to consult any physicians or physiotherapists because of their knee pain. They will be advised to continue participating in physical activity as long as: (a) their pain is no higher than 30 mm on a 100 mm VAS during the activity, (b) their knee pain does not outlast the physical activity, and (c) there is no strong increase in symptoms post activity. Participants will be told to register any use of analgesic or anti-inflammatory substances.

### Outcomes

As we are most interested in the exercise dose performed by the participant our primary outcome will involve TUT. We will also collect a range of secondary outcomes pertaining to the exercise dose, such as, number of repetitions, pulling force achieved during each repetition, and muscle strength. The exercises being performed have been shown to change condition status and so we will collect measures of pain, disability and a global rating of change, but these are secondary to our primary goal of evaluating the effects of feedback on TUT. The schedule for assessments is found in the SPIRIT figure (Table 2).

**Table 2 Tab2:**
[figure not shown]
SPIRIT figure. Schedule of enrolment, interventions and assessments

Primary outcome:Mean deviation from the prescribed TUT per repetition in seconds during the course of the intervention. The mean deviation is calculated as the difference between actual TUT and prescribed TUT per repetition (8 s). E.g. if the actual TUT is 6.5 s, the deviation is 1.5 s for this repetition. This is chosen as the primary outcome as TUT plays a large role in the total training dosage [21, 23–25] and adolescents have previously shown difficulties performing exercises with the prescribed TUT (Rathleff et al. *in review*).

Secondary outcomes:The total number of repetitions performed during the intervention period.Pulling force exerted per repetition measured in kilos. This will be expressed as the maximum pulling force during each repetition and corresponds to the resistance used when calculating training volume [26].Isometric strength (presented as Nm/kg) of knee extension, hip extension and hip abduction. Isometric strength will be collected at baseline and follow-up and will be used to explore the association between total exercise dose and changes in isometric strength. Isometric strength will be recorded at baseline and post intervention using a dynamometer (Commander PowerTrack, JTECH Medical, Midvale, Utah, USA) and will follow the protocol by Rathleff et al. [27] for knee extension (ICC= > 0.92). The test for hip abduction and hip extension will follow the test positions of the side-lying hip abduction (ICC = 0.76) and the hip extension with a short lever (ICC = 0.81) described by Thorborg et al. [28].Pain measured on a 100 mm VAS, where 0 mm is no pain and 100 mm is worst pain imaginable. The participants will enter their rating of pain intensity into the BandCizer™-app before and after each exercise. Pain is chosen as an outcome measure to investigate if the participants are more likely to comply to exercises that cause less pain.Kujala Patellofemoral Scale-score (0-100 score, with 0 as complete disability and 100 as fully functional). The Kujala Patellofemoral Scale is a frequently used validated outcome measure in PFP [19, 29, 30] however, it does not come in a Danish version. Therefore a Danish translation has been made with the same content and wordings as the original English version and a backwards translation to English was made according to principles of the translation of patient-reported outcome measures [31], however the translation has not been published. Kujala will be collected at baseline and at follow-up.Global rating of change at follow-up. This will be used to measure the participants’ self-reported recovery on a 7-point Likert scale ranging from “much improved” to “much worse”. Participants are categorised as improved if they rate themselves as “much improved” or “improved” (category 6-7) and categorised as not improved if they rate themselves from “slightly improved” to “much worse” (category 1-5). A 7-point Likert scale to assess self-reported change from baseline has previously been used in studies resembling this study [7, 19].

### Sample size and power considerations

It is expected that the feedback group will have a TUT close to the recommended 8 s per repetition whilst the control group will have a TUT of 6.5 s which is close to the results of an unpublished study (Rathleff et al. *in review*). Based on a standard deviation of 1.22, which was found in the before-mentioned study, and a two-sided 5 % significance level and a power of 80 %, a sample size of 15 participants per group will be necessary. Taking into consideration possible drop-outs, we will include a total of 40 participants.

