### Randomisation

Forty adolescents diagnosed with PFP will be block randomized in block sizes of 2 to 8 (1:1) into 2 parallel groups of 20 participants using a random number generator on www.random.org. A researcher not involved in the study will generate the allocation sequence and is the only person who will know the block sizes. In practice, after all baseline measurements have been made, the primary investigator will take a sequentially numbered opaque sealed envelope in which allocation to either the feedback group or the control group has been previously determined.

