### Statistical analysis

All statistical analyses will be performed according to a pre-established analysis plan. IBM SPSS Statistics ver. 23 will be used as statistical software. The primary analysis will test the between-group difference of the mean deviation from the prescribed TUT per repetition using an unpaired *t*-test. Secondary analyses will test total repetitions, total pulling force per exercise, isometric strength and Kujala Patellofemoral Scale using an unpaired *t*-test. The relative risk (RR) will be calculated for the dichotomized global rating of change to determine the probability of being improved and a Z-test will test the proportion of repetitions that are performed with the prescribed TUT compared with the proportion of repetitions that deviate from the prescribed TUT. Explorative analyses using Pearson’s correlation coefficient will be performed to test: (a) the association between pain and compliance to a specific exercise, and (b) the association between total exercise dose and isometric strength progression.

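### The 15 per group given for 80% power does not follow from the printed figures, which need 12; 15 per group gives about 90% power

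*Protocol article*

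**What the plan says.** The sample size section of the protocol article expects that "the feedback group will have a TUT close to the recommended 8 s per repetition" and that "the control group will have a TUT of 6.5 s". The calculation is "Based on a standard deviation of 1.22", which the section attributes to an unpublished study, with "a two-sided 5 % significance level" and 80% power. From these it concludes that "a sample size of 15 participants per group will be necessary". A separate sentence then raises the total to 40 to allow for drop-outs, without giving a rate.

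Three other sections supply the rest of the calculation:

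- **Test.** The statistical analysis section says: "The primary analysis will test the between-group difference of the mean deviation from the prescribed TUT per repetition using an unpaired" t-test.
- **Allocation.** The randomisation section says that participants will be "block randomized in block sizes of 2 to 8 (1:1) into 2 parallel groups of 20 participants".
- **Deviation scale.** The definition of the primary outcome works an example: "if the actual TUT is 6.5 s, the deviation is 1.5 s for this repetition".

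**The concern.** The section prints two expected means, a standard deviation, a significance level, a power and a sample size. A reader should be able to get from the first four and the power to the sample size. Taking the feedback mean as 8 s, the standardised difference is above 1.2. A difference that large needs fewer than 15 per group at 80% power.

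What is at stake is whether the planning statement can be reproduced. A reader cannot tell whether the trial was sized for 80% or 90% power, or for 1.5 s or something smaller. Anyone who judges the result against the planned difference, or reuses these figures for a later trial, needs to know.

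**Working it through.** **Inputs**

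| Input | Value | Where |
|---|---|---|
| Feedback mean TUT | 8 s (worded as close to 8 s) | Sample size section |
| Control mean TUT | 6.5 s | Sample size section |
| Difference, feedback mean taken as 8 s | 8 − 6.5 = 1.5 s | Arithmetic |
| Standard deviation | 1.22 s | Sample size section |
| Significance level | 5%, two-sided | Sample size section |
| Power | 80% | Sample size section |
| Test | Unpaired t-test | Statistical analysis section |
| Allocation | 1:1 | Randomisation section |

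**Step 1: try to reproduce 15 per group.** The standardised difference is d = 1.5/1.22 = 1.2295.

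Normal approximation: n = 2(1.96 + 0.8416)²/d² = 2 × 7.849/1.5117 = 10.4, so 11 per group.

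Exact two-sample t-test (noncentral t, 2n − 2 degrees of freedom, noncentrality d√(n/2)): solving for 80% power gives n = 11.43, so 12 per group. The stated 15 is not reproduced. It is 3 per group above the requirement, or 15/12 = 1.25 times it.

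**Step 2: power at fixed group sizes (t-test, 1.5 s, SD 1.22).**

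| Per group | Power |
|---|---|
| 11 | 78.3% |
| 12 | 82.1% |
| 14 | 87.9% |
| 15 | 90.1% |
| 20 | 96.6% |

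**Step 3: does another standard method give 15 at 80% power?**

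| Variant | Per group |
|---|---|
| One-sided 5%, normal approximation | 9 |
| Normal approximation with Guenther's correction (11.34) | 12 |
| Mann-Whitney, efficiency 0.955 (11.43/0.955 = 11.97) | 12 |
| Mann-Whitney, efficiency 0.864 (11.43/0.864 = 13.23) | 14 |
| t-test, two-sided 2.5% (13.91) | 14 |
| t-test, two-sided 1% (17.18) | 18 |

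None does.

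**Step 4: which single change gives 15?**

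- *Power.* With every other input as printed, 90% power needs 14.93, so exactly 15.
- *Difference.* With SD 1.22 and 80% power, a difference of 1.3 s (a feedback mean of 7.8 s) needs 14.85, so 15. The exact boundary is 1.293 s; at 1.29 s the requirement is 15.06, so 16.
- *Standard deviation.* With 1.5 s and 80% power, SD 1.41 needs 14.89, so 15. The exact boundary is 1.415; at 1.42 the requirement is 15.09, so 16.

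**Step 5: could drop-out be the explanation?** Inflating 12 for 20% loss gives 12/0.80 = 15. But no 20% rate is stated, and the text makes its drop-out allowance after the 15, in going from 30 (2 × 15) to 40.

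**The case against.** The strongest reply is that 1.5 s is an inference. The section prints no between-group difference and places the feedback mean only close to 8 s. The 1.5 s in the outcome definition illustrates the deviation for one repetition and is not a planning difference. If the authors calculated with about 7.8 s, then the standard deviation, power and 15 per group are all right as printed, and only the exact difference is missing.

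This stands as far as it goes. A reader might infer from the mismatch that at least one printed planning figure must be wrong. The document does not support that, because an unprinted feedback mean near 7.8 s would remove the conflict. Equally, no such value appears anywhere. The only numbers given for the two means are 8 and 6.5, and on those the stated result does not follow.

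A second reply is that the error is harmless, because 15 exceeds 12 and 20 per group will be randomised. That also stands for power: 96.6% at a 1.5 s difference and 90.7% at 1.3 s with SD 1.22, both before drop-out. A reader who sees a faulty sample size might suspect an underpowered trial, and these figures point the other way. They limit how serious the error is, but the sentence still does not agree with its own inputs.

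It may also be said that an article condenses a fuller document. That excuses missing detail. Here the figures are printed and do not agree.

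**Conclusion.** The point holds in a limited form. The printed figures, with the feedback mean taken as 8 s and the unpaired t-test, need 12 per group for 80% power. The stated 15 gives 90.1%, about 10 percentage points more than claimed.

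The exact match at 90% power makes a misreported power a natural guess, but it is not proof. An unstated difference of about 1.3 s or a standard deviation of about 1.41 would explain the 15 as well.

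The result assumes equal group sizes, a common standard deviation of 1.22 that applies to the participant-level means being compared, and a difference of exactly 1.5 s. The error is conservative on these figures. It is one of reporting and reproducibility, and gives no reason to question the enrolment target.

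**What to change.** Correct the sentence so that its figures agree, in whichever way matches the calculation that was done:

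- 12 per group for 80% power; or
- 15 per group for 90% power; or
- keep 15 per group and 80% power, and print the exact difference or standard deviation used.

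The cost is one sentence. The total of 40, the conduct of the trial and the analysis do not change.

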### Randomisation

Forty adolescents diagnosed with PFP will be block randomized in block sizes of 2 to 8 (1:1) into 2 parallel groups of 20 participants using a random number generator on www.random.org. A researcher not involved in the study will generate the allocation sequence and is the only person who will know the block sizes. In practice, after all baseline measurements have been made, the primary investigator will take a sequentially numbered opaque sealed envelope in which allocation to either the feedback group or the control group has been previously determined.

### Blinding

Participants will be told that the study is about adolescents with PFP and training with a new sensor, BandCizer™, that can give information about how they train, and that there will be two groups that use the BandCizer™-app in two different ways. They will not receive any information about the primary outcome measure or how the parallel group uses the app and will thus be blinded to the type of exercise feedback. The two groups will be training in separate group training sessions.

### Data collection and management

All data will initially be written on paper forms and afterwards entered into Microsoft Excel 2013 (Microsoft Corporation, Washington, USA) by the primary investigator at the study site where data originated. Data from BandCizer™ is uploaded from the iPad to an online server from where raw data on TUT, pulling force, repetitions and pain will be accessible only for the primary investigator. A visualisation of the data output from BandCizer™ is seen in Fig. 6. Prior to the statistical analyses data will be exported to IBM SPSS Statistics ver. 23 (IBM, New York, USA). Participants will complete all self-report data forms. All original paper forms and informed consent forms will be kept in a locked cabinet at the study site. All data will be kept for 10 years after completion of the study which in accordance with The European Code of Conduct for Research Integrity [32].

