## Methods

### Study design

This study, which is called the The XRCISE-AS-INSTRUcted-1 trial, is a randomized, controlled, participant-blinded, superiority trial, with a 2-group parallel design to be conducted in Aalborg, Denmark. The primary endpoint will be 6 weeks after an initial exercise instruction, using a summary of exercise dosage-data collected from 0 to 6 weeks. Reporting of this study will follow CONSORT guidelines for reporting parallel group randomized trials with the extension for non-pharmacological treatments and TIDieR for intervention description [16, 17]. Reporting of this protocol will follow the SPIRIT statement [18]. The study will be conducted at the Department of Occupational Therapy and Physiotherapy at Aalborg University Hospital in Denmark.

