### Withdrawal and adverse events

If a participant experiences an adverse event (e.g. an injury to the musculoskeletal system such as a muscle tear, a muscle strain, a sprained joint, injury from falling, DOMS that lasts for more than 48 h after performing the exercises or exacerbation of PFP) and is not able to perform the exercises, the participant will be able to withdraw from the study. The study may also be discontinued by participant request or withdrawal of informed consent. Data until the point of withdrawal will be included in the data analyses. If a participant experiences an adverse event and has to withdraw, data until the last training before the adverse event occurred will be included in the analyses. The participants are instructed to report any adverse events to the primary investigator as quickly as possible either by e-mail, SMS, phone call or during the supervised training sessions. The primary investigator will then ask the participant if the event occurred when they performed the exercises or during other activities. If the event occurred during the exercises the primary investigator will report the incident to the sponsor as quickly as possible and no later than 15 days after the participant reported the event. Sponsor will report adverse events to the Ethics Committee of North Denmark Region no later than 7 days after being informed.

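### Raw sensor data are reserved for one person who knows the allocation, so as written nobody blind to arm can derive or verify the step from raw data to the primary outcome

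*Protocol article*

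**What the plan says.** All places are in the Methods of the protocol article.

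- **Access.** Data collection and management: "raw data on TUT, pulling force, repetitions and pain will be accessible only for the primary investigator". No time limit is given. The paper-form data are "afterwards entered into Microsoft Excel 2013 (Microsoft Corporation, Washington, USA) by the primary investigator at the study site where data originated".
- **Allocation.** Randomisation: after baseline measurements, "the primary investigator will take a sequentially numbered opaque sealed envelope". The sequence itself comes from a researcher outside the study.
- **Contact.** Withdrawal and adverse events: "The participants are instructed to report any adverse events to the primary investigator as quickly as possible"; supervised sessions are one of the listed routes. Compliance and participant retention: if participants miss a session without cancelling, "they will be contacted by the primary investigator and asked in a friendly manner if they will return to the next group training session".
- **Blinding.** Study design: "This study, which is called the The XRCISE-AS-INSTRUcted-1 trial, is a randomized, controlled, participant-blinded, superiority trial, with a 2-group parallel design". The Blinding section describes what participants are not told and adds: "The two groups will be training in separate group training sessions". No blinding of an investigator, data handler or analyst is described.
- **Later access.** Access to the final trial data set: the primary investigator and all co-authors have the final data set before publication, and de-identified individual data become public within 6 months after it.

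**The concern.** The Strengths section puts the objective sensor first among the trial's merits. A sensor guards against biased measurement. It does not guard against choices made between the stored record and the number that enters the *t*-test. The usual protection for that step is that someone who does not know the arm makes the choices, or can repeat them.

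Here the access rule excludes everyone except a person who knows the arm. If the result is later questioned, nobody could show from within the described procedures that the primary-outcome data set was built in the same way in both arms.

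**Working it through.** The plan gives no figure for this point, so the check sets the sections side by side.

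1. **What the primary outcome is built from.** Outcomes defines it as the difference between actual TUT and the prescribed 8 s per repetition, averaged over the intervention. Actual TUT is among the raw server data.
2. **Who can reach those data.** The primary investigator alone (Data collection and management).
3. **Whether that person knows the arm.** Yes, in practice: the same person takes the envelope at allocation (Randomisation).
4. **Whether anyone else could do or repeat the step.** Steps 1 to 3 leave no one. An analysis plan could add handling rules or coded files. A second, allocation-blind person would still need the raw data, and the access rule denies that. The point therefore rests on a stated restriction, not on silence.
5. **Whether there are choices to make in that step.** At least two appear in the document.
   - *Cut-off.* Withdrawal and adverse events sets two limits. After an ordinary withdrawal, data count up to the withdrawal. After an adverse-event withdrawal, they count only up to the last training before the event. How a withdrawal is classed and dated decides which sessions count, and events are reported to the primary investigator.
   - *Imputation.* Analysis population and missing data fills the rest of a drop-out's intervention with that participant's own mean so far, so the cut-off also sets the imputed part. A participant with no repetitions receives the group mean.
6. **How many participants these rules could touch.** Sample size and power considerations needs 15 per group and enrols 40, leaving room for 40 − 2 × 15 = 10 drop-outs, or 10/40 = 25%. This is the allowance in the plan, not a forecast and not a bias.
7. **Whether later access closes the gap.** Only in part. Co-authors and the public receive the final data set, which lies after the step in question. Access to the raw server files is not stated for them.
8. **How far removing arm labels would help.** The plan expects a TUT of about 8 s with feedback and 6.5 s without, with SD 1.22 s: (8 − 6.5)/1.22 = 1.23 SD. Someone inspecting individual records could often guess the arm. Rules fixed in advance and run by script therefore matter more than masked labels alone.

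**The case against.** **Extraction may be automatic.** The Background says the device measures repetitions, TUT and pulling force, and the server data are listed under those same names. They may already be device output. This stands. A reader might infer that the investigator marks repetitions by hand while knowing the arm, but no section says so. The document does not even name who derives or analyses the outcome. The cut-off and imputation choices remain either way.

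**The rules may be in the analysis plan.** Statistical analysis refers to a plan set in advance, which is not shown and may well fix handling rules or coded files. That stands too, and the absence of such rules here is not the point. The exclusive access rule is in the text and would still have to change.

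**The restriction may be a confidentiality measure.** That is plausible. Adding one co-author need not weaken it.

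**Steering of participants.** A reader might infer that the investigator would watch accruing TUT and encourage participants accordingly. The documents do not support this as a demonstrated route. The contacts described follow an uncancelled missed session or a participant's own report, not sensor data. Both groups are told that TUT is part of compliance. Whoever supervises the separate weekly sessions sees arm and performance directly, and closing the server would not alter that. The supervising physiotherapist is not expressly identified as the primary investigator.

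**There is some independent check.** Correct for the final data set, so it would be too broad to say that nothing can be checked. The gap is confined to the step before it.

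**Conclusion.** The point holds in a limited form. As the protocol article stands, no allocation-blind person can derive or verify the step from raw sensor data to the primary-outcome data set, because the raw data are reserved for one person who knows the arms. This rests on two readings: that taking the envelope means knowing the allocation, and that the access rule applies as worded throughout.

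The size of any bias cannot be estimated. A reader might try to express it in seconds by assuming that some share of spurious pulls is kept in one arm and not in the other. The document gives no input for such a share or for the length of such pulls, so the result would only return the assumption. Nothing here shows that the outcome is, or will be, derived with bias. The point is a safeguard worth adding because it is cheap, not an error that invalidates the design.

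**What to change.** 1. Amend Data collection and management so that an existing co-author also has raw-data access, preferably one without participant contact. The document does not say which co-authors meet that condition, so the team must name one.
2. Derive repetitions and TUT with one fixed script, applied identically to files carrying study numbers only. Fix the handling rules beforehand, including the adverse-event cut-off and the imputation after drop-out. The group-mean imputation needs only a coded label, A or B.
3. Lock the primary-outcome data set and run the primary *t*-test as group A v group B before the arm code is opened.
4. Where feasible, limit the primary investigator's view of accruing TUT data to confirming that uploads arrive.
5. State in the text whether extraction is automatic and who performs it.

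The cost is a change of server rights, a short amendment and a little extra data handling. Sample size, visits and intervention are unaffected. The downside is that the primary investigator cannot look up TUT data during the trial. The document attaches no decision to such a look-up: adverse events are reported directly, and no stopping rules are planned.
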